### Assignment to screening strategies

2.6

Since randomization is not possible in the emulation of target trials, men will be assigned to the screening strategy in each of the trials based on their observational data. Considering that the intention of the PSA test is not recorded in the register, additional measures will be taken to ensure proper capture of the PSA-based screening instead of diagnostic PSA testing. Men who have had an immediate diagnosis following their PSA test (ascertained as within 6 mo from the test), and the diagnosis showed distant metastasis (M1) or the diagnosis was prompted by urinary or other symptoms, the PSA test will not be classified as a PSA-based screening test. If the PSA test was preceded by urological symptoms or bone pain within 6 mo in the patient register, the test will not be classified as a PSA-based screening test. Moreover, we will not consider men as screened if they underwent a PSA test, but have no record of PCa diagnosis in the registers, yet died from PCa within 6 mo of the PSA test. We will assume that the adjustment for the confounders is sufficient to mimic the randomization in the target trial (ie, we assume that they are randomly assigned within the levels of the confounders). Considering the observational nature of the study, blinding is not possible, and the men will be aware of their screening activity.

Figure 1A illustrates the flowchart of the inclusion into the trial based on the main analysis design.

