### Eligibility criteria

2.3

Men aged 75–79 yr between 2007 and 2023, with no PCa diagnosis at the time of inclusion (based on each trial emulation), will be considered eligible for the trials. To ensure proper control for potential confounding and to be able to evaluate the eligibility criteria, only men with complete information on their screening status, outcomes, and confounders in the registers will be included. The summary number of the men excluded due to missing values will be described in the final study flowchart.

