### Main analysis—sequential design with the CSW approach based on age at enrollment

2.5

Emulated target trials assign men into one of the two screening arms based on their screening pattern during the eligibility period, which starts when they attain the age of interest for the study (75–79 yr) for the first time and every month thereafter (eg, at age 75 yr, 75.083 yr, 75.167 yr, and so on).

Screening is ascertained within the 1st month from trial initiation, representing the eligibility and assignment period. Eligible men with at least one PSA test in this period will be assigned to the screening arm. Those with no PSA test in this window will be assigned to the control arm. Assignment ascertainment is assumed to be accurate for all participants, as the STHLM0 contains the data on PSA testing for men living in Stockholm and who were tested in Stockholm since 2007 [22]. Considering the assumptions of causal inference frameworks [19], the following three principles are assumed to be fulfilled:1.Positivity: Every man living in Stockholm within the age group of interest has a nonzero chance of deviating from the protocol at any point during the assessment period, and every eligible man is assumed to have had the opportunity to undergo a PSA test.2.Consistency: The survival outcome we observe for the men under the given screening strategy is the same as the outcome that would have occurred if we had explicitly assigned these patients to follow the same strategy (ie, their potential outcome). As such, the screening protocol is assumed to have been defined clearly and applied consistently throughout the study period in our study. Moreover, we assume that the statistical models used in the analysis (described below) are specified correctly.3.Exchangeability: There are no unmeasured confounders; all factors that influence both the screening assignment and the likelihood of deviating from the protocol have been measured. We assume based on the confounders accounted for in the study (described below) that we address the potential factors that impact the screening assignment.

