#### Data preparation and choice of confounders

2.10.1

Data on all men living in Stockholm will be used, and ascertainment of time zero will be performed for all eligible men with no information on the variables necessary for the analysis missing. As men can continuously be eligible to be included in the sequential trials, the choice of time zero will follow the recommendation of Hernán et al [17], and emulation will be done repetitively during the eligibility period between 2007 and 2023. The confounders of interest are age (continuous), trial year (categorical; from 2007 to 2023), country/region of birth (categorical; Sweden, Nordic, European Union, and others), income (categorical; five quintiles), previous hospitalization during the past year (yes/no), number of hospitalizations during the past year (continuous), number of outpatient specialized health care visits (continuous), non–age-adjusted Charlson Comorbidity Index (continuous, based on adaptations for register-based Swedish data [20], and cumulatively computed, based on the past 5 yr until the end of the previous calendar year before the assessment), education (categorical; ≤9 yr of formal education, 10–12 yr of formal education, and ≥12 yr of formal education), civil status (categorical; not married, married, divorced, and widowed), current cancer diagnosis excluding PCa (yes/no), and family history of PCa (yes/no, based on father, brother[s], or son[s] diagnosed with PCa).

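### Men in hospital at time zero stay eligible and admission is adjusted for only over the past year, so acute illness may confound the mortality contrast, mainly in the early years

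*Protocol article*

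**What the plan says.** All references are to the protocol article.

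- **Eligibility (2.3).** Men aged 75–79 "with no PCa diagnosis at the time of inclusion (based on each trial emulation), will be considered eligible for the trials", given complete data. Being in hospital is not an exclusion.
- **Assignment (2.5).** A new trial starts every month. "Eligible men with at least one PSA test in this period will be assigned to the screening arm".
- **Classification of tests (2.6).** The stated aim is that "additional measures will be taken to ensure proper capture of the PSA-based screening instead of diagnostic PSA testing". The reason for testing is inferred by rule: "Considering that the intention of the PSA test is not recorded in the register". A test is not screening if a prostate cancer diagnosis follows within 6 months and "the diagnosis showed distant metastasis (M1) or the diagnosis was prompted by urinary or other symptoms". The same holds for "If the PSA test was preceded by urological symptoms or bone pain within 6 mo in the patient register", and for a man with no recorded prostate cancer diagnosis who "yet died from PCa within 6 mo of the PSA test".
- **Adjustment (2.10.1).** The admission covariates are "previous hospitalization during the past year (yes/no") and the number of admissions over the same year. The list also has specialist outpatient visits, current cancer other than prostate cancer, and a Charlson index that stops at the end of the previous calendar year. Section 2.10.2 uses this list for the censoring weights.
- **Data (2.2).** Hospitalization is among the linked register data.

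**The concern.** A man in hospital is not facing an ordinary screening decision, and his short-term mortality is likely to be raised. His illness may also change his chance of a PSA test: a work-up for weight loss or a suspected cancer of unknown origin may raise it, and other acute illness may lower it. If such a man has no recorded urological symptoms or bone pain and no prostate cancer is found, his test passes every rule in 2.6 and counts as screening.

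The admission covariates do not separate a current inpatient from a man with the same number of stays who was discharged eleven months ago. The Charlson index is lagged, so it does not register a new acute illness.

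At stake is the exchangeability assumed in 2.5 and 2.6. Any imbalance would act on all-cause mortality and would be strongest early. Section 2.10.4 reports the difference in cumulative incidence at 5, 10 and 15 yr, and the 5-yr figure is the most exposed.

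**Working it through.** **1. Do the stated rules cover care setting?** The three rules in 2.6 depend on prostate cancer features, on recorded urological symptoms or bone pain, or on prostate cancer death. None depends on admission. Section 2.3 has no inpatient exclusion, and 2.10.1 has no term for a current or recent stay. The gap is in the text.

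**2. The plan's own scale.** Section 2.12 assumes 35 000 deaths, 20% screened and cumulative mortality of 0.80 after 17 yr. For HR 0.956, taking two-sided alpha 0.05 (an assumption, as none is stated):

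Power = Φ(|ln 0.956| × √(35 000 × 0.2 × 0.8) − 1.96) = Φ(0.0450 × 74.83 − 1.96) = Φ(1.41) = 92.0%, as in Table 1.

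The effects in Table 1, 1.0 to 3.0 points, are 17-yr quantities.

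**3. Illustrative bias at 1 yr.** The document gives none of the inputs, so all are assumptions:

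- 25% of men have a past-year stay.
- Monthly admission *a* is 1–1.5% without and 6–8% with a past-year stay.
- 2% of men are tested per month in each stratum.
- Excess 1-yr mortality after an admission is 6–10 points.
- Admitted men are tested *r* times as often as others.

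In each stratum, with *t* = 0.02 / (1 − *a* + *ra*):

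- share admitted among tested = *ra* / (1 − *a* + *ra*)
- share admitted among untested = *a*(1 − *rt*) / 0.98

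Bias = difference in shares, averaged 75%/25% over the strata, × excess mortality.

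Upper inputs with *r* = 2:

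- No past-year stay (*a* = 1.5%): 2.96% − 1.47% = 1.49%
- Past-year stay (*a* = 8%): 14.81% − 7.86% = 6.95%
- Average: 0.75 × 1.49 + 0.25 × 6.95 = 2.85%
- Bias: 2.85% × 10 points = 0.29 points

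| *r* | Bias at 1 yr, points (positive = against screening) |
|---|---|
| 0.5 | −0.07 to −0.15 |
| 1.5 | +0.06 to +0.15 |
| 2 | +0.13 to +0.29 |
| 3 | +0.24 to +0.54 |

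**4. What is left later.** Mortality of 0.80 at 17 yr under a constant hazard gives λ = −ln(0.2)/17 = 0.0947 per yr. If the excess ends after year 1, the factor at *T* yr is exp(−0.0947 × (*T* − 1)).

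| *T* (yr) | Factor | 0.29 becomes | 0.54 becomes |
|---|---|---|---|
| 5 | 0.685 | 0.20 | 0.37 |
| 10 | 0.427 | 0.12 | 0.23 |
| 15 | 0.266 | 0.08 | 0.14 |
| 17 | 0.220 | 0.06 | 0.12 |

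A lasting excess hazard would shrink less.

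**5. Would refusing to count in-hospital tests solve it?** In the limiting case no admitted man counts as screened (*r* = 0). The shares then differ by −2.30% (lower inputs) or −3.19% (upper inputs), and the bias is −0.14 (× 6 points) to −0.32 (× 10 points). That favours screening and is about as large as the +0.13 to +0.29 at *r* = 2. The reason is the cloning in 2.10.2: the screening clone of a man admitted during the month would be censored and his control clone kept.

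**The case against.** The strongest reply is that this is a hypothesis. Nothing in the document says how many PSA tests are taken in hospital or whether admitted men are tested more or less often, so the bias could have either sign. This stands.

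A reader might infer that acute illness does bias the result, or that it could cancel the effects in Table 1. The document supports neither. More extreme assumptions do give large figures: 20% of tested against 1% of untested person-months in hospital, with 20 points of residual excess mortality, gives 0.19 × 20 = 3.8 points. Those shares have no more basis in the text than the smaller ones, and early excess deaths should not be compared with a 17-yr reduction.

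The calculation also stratifies on past-year admission alone. The number of stays, outpatient visits, current other cancer and the Charlson index adjust further, and the symptom rules in 2.6 remove some inpatient tests. This also stands, and it points to a smaller bias.

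A reader might take 3.3 as claiming that all-cause mortality is robust in general. It says only that misclassified cause of death does not affect it, and it concedes residual confounding.

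The disclosure in 3.3 and the array analysis in 2.11.2 answer less. They concern unmeasured factors, whereas admission is measured and linked. Nor is this a detail left to a fuller plan: the article states its eligibility rule, classification rules and confounder list, and the point concerns what they say.

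**Conclusion.** The point holds as a possible source of confounding that data already linked could reduce. Current inpatients are eligible, and the adjustment does not distinguish them from men admitted months earlier. The effect, if any, falls mainly on early results such as the 5-yr difference.

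On the assumptions shown, the bias is from under a tenth to about half a point at 1 yr, in either direction, and roughly 0.1 point or less at 15 to 17 yr if the excess mortality is confined to the first year. None of this is an estimate from the document. It justifies a cheap improvement, not a claim that the planned contrast is invalid.

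**What to change.** - **2.3:** at each monthly time zero, exclude from both arms men who are inpatients or were discharged in the previous 30 days. They may re-enter later monthly trials.
- **2.10.1:** add a recent-admission term, for example the last 90 days, to the screening and censoring weight models.
- **Reporting:** show results with and without the exclusion.
- **2.6:** do not reclassify in-hospital tests as non-screening in the main analysis, for the reason in step 5 of the working. If this is examined, make it a sensitivity analysis that treats admissions within the month alike in both arms, for example by censoring both clones at admission, with weights.

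The cost is plan wording and a date match in linked data, a small loss of person-months, and results that do not apply to men in hospital or just discharged. The exclusion and the 90-day term are fixed at time zero, so admissions that begin later in the month remain; only the sensitivity analysis addresses those.

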### Follow-up period

2.7

Men will initiate their follow-up based on the time of inclusion, starting from January 1, 2007, and end their follow-up by December 31, 2023, or if they experience the outcome of interest, whichever occurs first. The last recruitment age is 79.91 yr. The date of inclusion (time zero) will depend on the trial design; in the main analysis, this will be the date of age attainment.

### Outcomes

2.8

The first outcome of interest is all-cause mortality, which will be based on the reported date of death. The second outcome of interest is PCa-specific mortality, which will be ascertained based on the leading cause of death. The International Classification of Disease tenth revision is used to report the cause of death, and the code C61 is used to identify PCa-specific mortality. Men who are alive by December 31, 2023 will be censored by reaching the end of the follow-up period.

### Causal contrasts of interest

2.9

This study will consider an observational analog of an intention-to-screen analysis, comparing the screening strategies assigned during the ascertainment period. The no screening (control) arm will be used as the reference group in all analyses.

### Statistical analysis plan

2.10

#### Data preparation and choice of confounders

2.10.1

Data on all men living in Stockholm will be used, and ascertainment of time zero will be performed for all eligible men with no information on the variables necessary for the analysis missing. As men can continuously be eligible to be included in the sequential trials, the choice of time zero will follow the recommendation of Hernán et al [17], and emulation will be done repetitively during the eligibility period between 2007 and 2023. The confounders of interest are age (continuous), trial year (categorical; from 2007 to 2023), country/region of birth (categorical; Sweden, Nordic, European Union, and others), income (categorical; five quintiles), previous hospitalization during the past year (yes/no), number of hospitalizations during the past year (continuous), number of outpatient specialized health care visits (continuous), non–age-adjusted Charlson Comorbidity Index (continuous, based on adaptations for register-based Swedish data [20], and cumulatively computed, based on the past 5 yr until the end of the previous calendar year before the assessment), education (categorical; ≤9 yr of formal education, 10–12 yr of formal education, and ≥12 yr of formal education), civil status (categorical; not married, married, divorced, and widowed), current cancer diagnosis excluding PCa (yes/no), and family history of PCa (yes/no, based on father, brother[s], or son[s] diagnosed with PCa).

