### Study population and data source

2.2

This study and the target-trial emulation will use population-based register data of men living in Stockholm between 2007 and 2023, who were screened for PCa, extracted from the Stockholm Prostate Cancer Diagnostics Register (STHLM0), a comprehensive register of all men tested for PCa with PSA in Stockholm, Sweden [22]. The STHLM0 has complete PSA test records since January 1, 2007 [22]. This will be supplemented with information on nontested men from the STHLM0+ register [22]. Demographic information, family history of PCa, diagnoses, hospitalization, specialized outpatient health care, PCa treatment, and mortality information are provided from the linked Swedish population registers [22]. Figure 1 illustrates the flowchart of inclusion into the target-trial emulation.

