### Potential strengths and limitations

3.3

Our study will leverage the STHLM0, which has near complete information on all PSA tests in Stockholm, with linkage to national Swedish registers allowing the capture of diverse lists of potential confounders [22]. In our planned study, we consider the emulation of pragmatic target trials suitable for addressing the research questions at hand. Moreover, the potential follow-up of up to 17 yr can provide sufficient time for the relevant outcomes to occur. Henceforth, this work has the potential to guide decisions on PCa screening cessation, addressing an important need among men who undergo opportunistic testing despite the lack of guidelines for this age group.

Despite these considerations, the study has potential limitations. First, our analysis plan assumes adherence to the assigned arm at each trial, which might not be ideal. Some of the men who will be considered as screened might have been prompted to undergo a PSA test following the symptoms of metastasis or urinary retention. However, the cause of the PSA test cannot be discerned from the register data. The diagnosis if preceded by symptoms is captured in the register but has incomplete information [39]. Additionally, men who underwent a PSA test within the study period due to health checkup following previously elevated tests are classified as screened in the study. However, due to the shift to organized PCa testing [40], this approach might better reflect future screening directions of continuing screening in this age group that was initiated at an earlier age, instead of initiating screening in this age group. Second, unmeasured and residual confounding cannot be ruled out, and data on functionality, holistic objective health status, and disability are not available from the registers. Although we attempt to conduct a subgroup analysis based on the level of multimorbidity excluding those who are sickest, it would not granularly capture individual causes of the PSA testing. Additionally, men who are institutionalized might not have admission or usage of specialized outpatient care, underestimating their multimorbidity.

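### PSA history is missing from the confounder list, so men tested to follow up an earlier raised PSA will be over-represented in the screening arm with only indirect control

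*Protocol article*

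**What the plan says.** All references are to the protocol article.

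- **Adjustment set (§2.10.1).** It opens "The confounders of interest are age (continuous), trial year (categorical; from 2007 to 2023", continues through birth region, income, hospitalization, specialized outpatient visits, Charlson index, education, civil status and other cancer, and closes with "family history of PCa (yes/no, based on father, brother[s], or son[s] diagnosed with PCa". It has no earlier PSA test, time since last test or PSA value.
- **Where the set is used.** The censoring weights are built from this list (§2.10.2). The standardization runs over the confounders, and no further covariates are named for the screening weights (§2.10.4).
- **Eligibility (§2.3).** Men aged 75–79 "with no PCa diagnosis at the time of inclusion (based on each trial emulation), will be considered eligible for the trials", given complete data. Earlier PSA tests play no part.
- **Filter on diagnostic tests (§2.6).** A test is declassified if it falls under "If the PSA test was preceded by urological symptoms or bone pain within 6 mo in the patient register", if it is followed within 6 months by a metastatic or symptom-prompted diagnosis, or if prostate cancer death follows within 6 months without a recorded diagnosis. An earlier raised PSA is not a criterion.
- **Data held (§2.2).** "The STHLM0 has complete PSA test records since January 1, 2007".
- **Classification (§3.3).** Men tested "due to health checkup following previously elevated tests are classified as screened in the study", on the ground that "this approach might better reflect future screening directions of continuing screening in this age group that was initiated at an earlier age".
- **Assumption (§2.5).** Exchangeability is taken to hold because "all factors that influence both the screening assignment and the likelihood of deviating from the protocol have been measured".

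**The concern.** A man whose PSA was raised earlier is more likely to be tested again in a given month; §3.3 itself describes such tests. He is also plausibly at higher risk of dying of prostate cancer. That makes PSA history a common cause of assignment and outcome, and the register records at least the testing part of it.

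Cloning makes the two arms identical at time zero, but artificial censoring during the one-month window undoes this. The clones left in the screening arm are the men who tested, and those left in the control arm are the men who did not. Only the weights and the outcome model can restore balance, and both work from a list without PSA history.

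The hypothesis in §2.1 is a modest survival benefit through lower prostate cancer mortality. An excess of monitored men among the screened could hide or reverse it. §3.1 says that a finding of no benefit or of harm should lead guidelines to consider a stronger recommendation against screening after 74, so the consequence is practical.

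**Working it through.** **The plan's own figure.** The only quantitative benchmark is the all-cause power table (§2.12). Take 35 000 deaths, 20% screened, HR 0.956 and two-sided α = 0.05 (assumed, since α is not stated). The Schoenfeld formula gives z = √(35 000 × 0.2 × 0.8) × |ln 0.956| − 1.96 = 74.83 × 0.0450 − 1.96 = 1.41, a power of 92.0%, as stated. The present point does not depend on this figure; it serves below as a yardstick.

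**Inputs for the illustration.** The documents give no share of men under monitoring, no monthly testing rates and no mortality by PSA history. All values below are assumptions.

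**Calculation 1: mixture of monitored and other men, no true screening effect.** Let m be the share monitored, q₁ and q₀ the monthly testing probabilities in monitored and other men, and r₁ and r₀ their 10-year prostate cancer mortality.

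- Share monitored in the screening arm: s₁ = m·q₁ / [m·q₁ + (1−m)·q₀]
- Share monitored in the control arm: s₀ = m(1−q₁) / [m(1−q₁) + (1−m)(1−q₀)]
- Mortality ratio: [s₁r₁ + (1−s₁)r₀] / [s₀r₁ + (1−s₀)r₀]

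For m = 0.10, q₁ = 1/12, q₀ = 0.015:

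- s₁ = 0.00833 / (0.00833 + 0.0135) = 38.2%
- s₀ = 0.0917 / (0.0917 + 0.8865) = 9.4%
- r₁ = 4%, r₀ = 1.5%: 2.45% / 1.73% = 1.42

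| m | q₁ | q₀ | r₁ vs r₀ | s₁ | s₀ | Ratio |
|---|---|---|---|---|---|---|
| 5% | 1/12 | 0.015 | 3% vs 1.5% | 22.6% | 4.7% | 1.17 |
| 10% | 1/12 | 0.015 | 3% vs 1.5% | 38.2% | 9.4% | 1.26 |
| 10% | 1/12 | 0.015 | 4% vs 1.5% | 38.2% | 9.4% | 1.42 |
| 15% | 1/6 | 0.015 | 6% vs 1.5% | 66.2% | 13.0% | 2.15 |

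**Calculation 2: array formula, the method that §2.11.2 proposes.** Bias factor = [p₁(RR−1)+1] / [p₀(RR−1)+1], where p₁ and p₀ are the prevalences of an earlier raised PSA in screened and unscreened men.

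| p₁ vs p₀ | RR 2 | RR 3 | RR 5 |
|---|---|---|---|
| 15% vs 5% | 1.10 | 1.18 | 1.33 |
| 30% vs 10% | 1.18 | 1.33 | 1.57 |

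Together the two calculations span about 1.1 to 2.1 (unrounded 1.095 to 2.149).

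**All-cause mortality.** At 30% vs 10%, an RR of 1.05 to 1.20 for the over-represented group gives factors of 1.010 to 1.039. On the log scale that is 0.0099/0.0450 = 22% to 0.0385/0.0450 = 85% of the effect at HR 0.956. If the over-represented group is instead healthier, an RR of 0.90 to 0.95 gives 0.980 to 0.990, the opposite direction. The sign of the net bias is therefore not determined.

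**The case against.** The strongest defence has four parts.

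1. **The classification is disclosed and reasoned.** §3.3 says that the emulated strategy is continued screening begun at a younger age. This stands as a choice of intervention. It does not bear on exchangeability: a continued-screening strategy still needs men with similar PSA histories who do and do not test in a given month.
2. **Some control exists.** The count of specialized outpatient visits may partly track urological follow-up. Comorbidity and socioeconomic covariates bear on healthy-tester bias. The §2.6 filter removes symptom-led tests, and §2.11.2 plans an array analysis for unmeasured confounding. A reader might infer from the omission that neither direction of bias is controlled at all; the documents do not support that. These measures are nevertheless indirect, and an array analysis is no substitute for adjusting for something on record.
3. **Monitored men are in both arms.** A reader might picture raised-PSA men in one arm and the rest in the other. With monthly entry, a man tested yearly falls in the control arm in most months. The problem is imbalance, not separation.
4. **The register's content has limits.** §2.2 refers to PSA test records; that values are held is implied, not stated. History before 2007 is not covered by the stated complete records. Number and recency of tests, however, need only dates.

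Leaving the matter to a fuller document is not a convincing answer, because §2.10.1 gives a list defined down to its categories and §2.10.2 relies on it.

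**Conclusion.** The omission is clear from the text and should be corrected before analysis. Followed as written, the plan leaves a common cause of testing and prostate cancer death out of the weights and the standardization, although at least its testing component is recorded.

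Confidence is high for the omission, not for the size. The 1.1 to 2.1 range for the prostate cancer mortality ratio under no true effect rests wholly on assumed inputs. It also takes the existing covariates and the symptom filter to remove none of the imbalance, so each scenario's figure lies towards its upper bound.

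A reader might also infer that the study is bound to be biased against screening. That goes too far. The illustration covers only the raised-PSA component for prostate cancer mortality; regular healthy testers pull the other way, and for all-cause mortality the net direction is uncertain.

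**What to change.** - Add to both weight models (screening and censoring), the outcome model and the standardization: number of PSA tests in the previous 2 years, time since last test, and last PSA value (spline or categories, with a *none on record* level). Confirm that the register supplies values; if not, use number and recency.
- For entries in 2007–2008, where a 2-year look-back is not available, use a *history not observable* category. This keeps those entrants and so the 15-year cumulative incidence difference in §2.10.4.
- Report results separately for men with and without a test in the previous 2 years.
- Use a January 2009 start only as a sensitivity analysis. With follow-up ending on 31 December 2023 it allows at most 15 years, which leaves essentially no one at risk at the 15-year time point.

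**Cost.** Test dates are already in the register, so the work is mainly data preparation. Two drawbacks remain. Look-back is limited for the earliest entrants. Positivity may also be strained for men tested very recently, who may have little chance of another test that month; this should be checked through the weight distribution.

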The actual capture of the outcome in PCa-specific mortality might be challenging to ascertain without autopsy among older men as the quality of the cause-of-death reporting decreases with age, and the death certificate might be suboptimal to capture PCa mortality among the oldest age group [[41], [42], [43]]. This observation has been reported in Nordic countries [42,44]. Thus, the sticky-diagnosis bias might affect determining whether PCa was the cause of death among the screened men compared with the nonscreened men [45]. As such, evaluation of both all-cause and PCa-specific mortality would be warranted, and this misclassification could affect PCa mortality, but not all-cause mortality [46]. A comparison of the risks among younger age groups can assist in ascertaining whether a potential difference in direction is due to the limitations of death certificates in older age and the sticky-diagnosis bias.

Although the study focuses primarily on mortality outcomes, diagnosis outcomes are addressed only descriptively, and the quality-of-life outcomes are not available in the registries. These findings would be needed for a fully informed decision-making process and subsequent updates to clinical guidelines.

Positivity is assumed as part of the emulation of target-trial design [47]. However, this might not be feasible in real life, as men who are very frail would be evaluated differently by health care providers and might not be considered for screening by the urologist as they might not be able to tolerate even conservative therapy.

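### The confounder list in 2.10.1 has no frailty measure, although the article says very frail men might not be considered for screening; a moderate residual imbalance could create much of the small all-cause effect sought

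*Protocol article*

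**What the plan says.** Section 2.10.1 lists the confounders in full. Apart from demographic and social variables and family history, health enters through "previous hospitalization during the past year (yes/no), number of hospitalizations during the past year (continuous), number of outpatient specialized health care visits (continuous"), other current cancer, and the Charlson index, which is "cumulatively computed, based on the past 5 yr until the end of the previous calendar year before the assessment". Sections 2.10.2 and 2.10.4 use the confounders for the censoring weights and the standardization; the screening weights rest on the same adjustment.

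Among its identifying assumptions, section 2.5 states: "There are no unmeasured confounders; all factors that influence both the screening assignment and the likelihood of deviating from the protocol have been measured".

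Section 3.3 says that "data on functionality, holistic objective health status, and disability are not available from the registers", accepts that residual confounding may remain, and notes that "men who are institutionalized might not have admission or usage of specialized outpatient care, underestimating their multimorbidity". In a remark on positivity it adds that "men who are very frail would be evaluated differently by health care providers and might not be considered for screening by the urologist".

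Section 2.2 describes the linkage: "Demographic information, family history of PCa, diagnoses, hospitalization, specialized outpatient health care, PCa treatment, and mortality information are provided from the linked Swedish population registers".

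**The concern.** A factor that lowers the chance of a PSA test and raises the risk of death confounds all-cause mortality. The article points to frailty as affecting who is considered for testing, and frailty can be expected to raise mortality. If frail men are under-represented in the screened arm after adjustment, that arm will live longer whether or not screening works. All-cause mortality is the outcome that Table 1 is powered for, and the effect sought is close to 1, so a modest bias matters.

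The listed health variables may not close the gap. Charlson stops at the end of the previous calendar year, so it can be up to about a year old at a monthly time zero. The contact counts are, on the article's own account, unreliable for institutionalized men. The Charlson index is itself built from register records, so a second diagnosis-based score looks feasible. That is an inference: the article does not mention such a score.

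The exchangeability statement in 2.5 also describes the factors to be controlled as those affecting assignment and deviation. The relevant set is the common causes of screening (or deviation) and death.

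**Working it through.** **1. The plan's own figure.** Table 1 gives 92.0% power for a hazard ratio (HR) of 0.956 with 35 000 deaths and 20% screened. With the Schoenfeld formula and two-sided alpha 0.05 (assumed; not stated):

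z = √(35 000 × 0.20 × 0.80) × |ln 0.956| − 1.96 = 74.83 × 0.0450 − 1.96 = 1.41, so power is 92.0%. This reproduces the table. The HR that is just significant is exp(−1.96/74.83) = 0.974.

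**2. Assumed inputs.** Frailty prevalence in unscreened men p0 = 10 to 30%, frailty mortality HR (HRf) = 1.5 to 3, true screening effect null. The gap d is what remains after the 2.10.1 adjustments.

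**3. Gap that gives an initial HR of 0.956.** For a binary confounder the spurious HR at the start of follow-up is [1 + (p0 − d)(HRf − 1)] / [1 + p0(HRf − 1)]. Solving for d:

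d = 0.044 × [1 + p0(HRf − 1)] / (HRf − 1)

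| HRf | p0 = 10% | p0 = 15% | p0 = 30% |
|---|---|---|---|
| 1.5 | 9.2 points | 9.5 | 10.1 |
| 2 | 4.8 | 5.1 | 5.7 |
| 3 | 2.6 | 2.9 | 3.5 |

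At HRf = 2, the just-significant 0.974 is reached at about 3 points: 0.026 × 1.10 / 1 = 2.9 for p0 = 10%.

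**4. Absolute scale.** The initial HR cannot be carried forward as a constant, because frail men die first and the imbalance shrinks. I used a mixture of frail and non-frail men with constant hazards, calibrated to the plan's 0.80 mortality at 17 years. The non-frail survival s at 17 years solves (1 − p0)s + p0·s^HRf = 0.20. At time t, s(t) = s^(t/17), and the spurious difference in the cumulative incidence function (CIF) is d × [s(t) − s(t)^HRf].

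Example with p0 = 10%, HRf = 2: s = 0.2170. At 10 years s(t) = 0.4071, so a 5-point gap gives 0.05 × (0.4071 − 0.1657) = 1.21 points. At 17 years it gives 0.05 × (0.2170 − 0.0471) = 0.85 points.

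| 5-point gap | 5 yr | 10 yr | 15 yr | 17 yr |
|---|---|---|---|---|
| p0 10%, HRf 2 | 1.15 | 1.21 | 0.96 | 0.85 |
| p0 15%, HRf 2 | 1.14 | 1.22 | 0.98 | 0.88 |
| p0 10%, HRf 3 | 1.89 | 1.71 | 1.23 | 1.05 |
| p0 15%, HRf 3 | 1.87 | 1.74 | 1.28 | 1.10 |

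The 5-year column depends on constant hazards. If the hazard instead rises with an assumed Gompertz slope of 0.1 per year, so that s(t) = s^[(e^(0.1t) − 1)/(e^1.7 − 1)], the same gaps give about 0.8 to 1.4 points at 5 years and 1.2 to 1.9 at 10 years. The 17-year column does not change.

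**5. Gap for a spurious 1.5 points at 17 years.** d = 0.015 / (s − s^HRf). For p0 = 10%, 15% and 30% this is 8.8, 8.6 and 7.9 points at HRf = 2, and 7.1, 6.8 and 5.9 at HRf = 3. At HRf = 1.5 and p0 = 10% it would be 13.1 points, more than the prevalence itself, so it cannot occur.

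**The case against.** The strongest reply has four parts.

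First, a reader might infer that a small imbalance alone could produce the full 1.5-point reduction. That is not supported. It treats the initial HR as constant for 17 years; step 5 shows that 6 to 9 points are needed even at HRf 2 to 3. The gap must also survive adjustment for hospitalizations, specialist visits, Charlson and other cancer, which will share information with frailty. This part stands and limits the size of the point.

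Second, a reader might infer that frailty drives who is tested, or that 2.5 and 3.3 contradict each other. Neither holds. Section 3.3 says only that very frail men might not be considered. Section 2.5 states an assumption, which 3.3 openly qualifies. What remains is loose wording in 2.5 that leaves death out.

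Third, the plan already probes the bias: an array analysis and a contrast with younger men (2.11.2), and a subgroup with Charlson index up to 10 (2.10.5). These show how sensitive the result is, but they remove no bias from the main estimate.

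Fourth, the direction is not settled. Section 3.3 concedes that some tests prompted by symptoms will count as screening, which would raise mortality in the screened arm. A diagnosis-based score is also a proxy, and the article says nothing of its validity in these registers. Both points stand.

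**Conclusion.** The point holds in a limited form. The adjustment set lacks a frailty measure that the linked diagnoses could probably support, for a factor the article itself connects to being considered for screening.

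Under the assumed frailty HR of 2 to 3, the imbalance needed to mimic the target is moderate on the hazard scale (about 3 to 6 points) and larger on the 17-year absolute scale (about 6 to 9 points). At the 5- and 10-year reporting times, a 5-point gap would produce a spurious difference of about 1.1 to 1.9 points with constant hazards. At a frailty HR of 1.5 the threat is much weaker.

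The documents do not show that such a gap remains after adjustment, nor that the net bias favours screening. The case for acting is that the effect sought is close to 1 and the change is cheap.

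**What to change.** In 2.10.1, add a diagnosis-based frailty score to the covariates used for the weights and the standardization. It could be the Hospital Frailty Risk Score or an ICD-10 code set listed in advance, taken from the linked inpatient and specialist outpatient diagnoses, with a look-back ending at each monthly time zero. Report the all-cause CIF difference with and without the score, so that readers can see how far the estimate moves.

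In 2.5, word exchangeability as an assumption of no unmeasured common causes of screening (or deviation) and death, and state that frailty is only partly measured.

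The cost is extra coding and one more covariate; no new data are needed. The score is an imperfect proxy and will miss institutionalized men without hospital contact, so some confounding will remain.
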